## Abstract

**Background:**

During pediatric cardiopulmonary resuscitation (CPR), vasoactive drug preparation for continuous infusions is complex and time-consuming. The need for individual specific weight-based drug dose calculation and preparation places children at higher risk than adults for medication errors. Following an evidence-based and ergonomic driven approach, we developed a mobile device app called Pediatric Accurate Medication in Emergency Situations (PedAMINES), intended to guide caregivers step-by-step from preparation to delivery of drugs requiring continuous infusion. In a prior single center randomized controlled trial, medication errors were reduced from 70% to 0% by using PedAMINES when compared with conventional preparation methods.

**Objective:**

The purpose of this study is to determine whether the use of PedAMINES in both university and smaller hospitals reduces medication dosage errors (primary outcome), time to drug preparation (TDP), and time to drug delivery (TDD) (secondary outcomes) during pediatric CPR when compared with conventional preparation methods.

**Methods:**

This is a multicenter, prospective, randomized controlled crossover trial with 2 parallel groups comparing PedAMINES with a conventional and internationally used drug infusion rate table in the preparation of continuous drug infusion. The evaluation setting uses a simulation-based pediatric CPR cardiac arrest scenario with a high-fidelity manikin. The study involving 120 certified nurses (sample size) will take place in the resuscitation rooms of 3 tertiary pediatric emergency departments and 3 smaller hospitals. After epinephrine-induced return of spontaneous circulation, nurses will be asked to prepare a continuous infusion of dopamine using either PedAMINES (intervention group) or the infusion table (control group) and then prepare a continuous infusion of norepinephrine by crossing the procedure. The primary outcome is the medication dosage error rate. The secondary outcome is the time in seconds elapsed since the oral prescription by the physician to drug delivery by the nurse in each allocation group. TDD includes TDP. Stress level during the resuscitation scenario will be assessed for each participant by questionnaire and recorded by the heart rate monitor of a fitness watch. The study is formatted according to the Consolidated Standards of Reporting Trials Statement for Randomized Controlled Trials of Electronic and Mobile Health Applications and Online TeleHealth (CONSORT-EHEALTH) and the Reporting Guidelines for Health Care Simulation Research.

**Results:**

Enrollment and data analysis started in March 2017. We anticipate the intervention will be completed in late 2017, and study results will be submitted in early 2018 for publication expected in mid-2018. Results will be reported in line with recommendations from CONSORT-EHEALTH and the Reporting Guidelines for Health Care Simulation Research .

**Conclusions:**

This paper describes the protocol used for a clinical trial assessing the impact of a mobile device app to reduce the rate of medication errors, time to drug preparation, and time to drug delivery during pediatric resuscitation. As research in this area is scarce, results generated from this study will be of great importance and might be sufficient to change and improve the pediatric emergency care practice.

**Trial Registration:**

ClinicalTrials.gov NCT03021122; https://clinicaltrials.gov/ct2/show/NCT03021122 (Archived by WebCite at http://www.webcitation.org/6nfVJ5b4R)

## Introduction

While many drugs can be directly injected without prior preparation, others require a fastidious and complicated preparation and dilution by nurses before administration as continuous infusions. During pediatric cardiopulmonary resuscitation (CPR), quick, accurate, and safe preparation and administration of intravenous (IV) vasoactive drugs for continuous infusion is both complex and time-consuming [1-3]. In some critical situations such as postcardiac arrest return of spontaneous circulation (ROSC) or septic shock, preparing those drugs is particularly challenging. Contrarily to adults, children require individual specific weight-based drug dose calculation and preparation. The lower dosing-error tolerance [4] places children at higher risk than adults for life-threatening errors [5-7]. Medication errors have been reported in up to 41% of pediatric resuscitations, the most common being incorrect medication dosage, found in up to 65% of cases [8]. Proper preparation and delivery of these drugs could favorably affect pediatric resuscitation outcomes.

In resuscitations, time is also a decisive success criterion. It is well established that during the first 15 minutes of pediatric resuscitation, survival and favorable neurological outcome decrease linearly by 2.1% and 1.2% per minute, respectively [9]. They are negatively affected by time to drug preparation (TDP) and time to drug delivery (TDD) [10]. In a study with adults in cardiac arrest, the chance of ROSC was decreased by 4% for every 1-minute delay in delivery of a vasopressor [11].

To address these problems, we followed an evidence-based and ergonomic approach [12] to develop an innovative and customizable mobile device app called Pediatric Accurate Medication in Emergency Situations (PedAMINES). This app was designed to support nurses and physicians step-by-step from order to delivery of a wide range of drugs in real time, including those requiring continuous infusion [13]. In a previous single center simulation-based randomized controlled trial, we have shown that medication errors reduced significantly from 70% to 0% by using PedAMINES when compared with conventional methods [14]. PedAMINES also dramatically reduced TDP and TDD. The purpose of this protocol is to investigate whether the use of PedAMINES might similarly reduce medication errors, TDP, and TDD in other university hospitals and in smaller hospitals where nurses and physicians are exposed to a much lower extent to pediatric resuscitations. Simulation was used as an investigational method to assess these outcomes. We hypothesize that PedAMINES might reduce medication errors and delays to TDP and delivery independently of the existing conventional preparation methods or nurse skills. We expect even bigger improvements in smaller hospitals due to strong disparities between nurses less exposed to pediatric resuscitations.

## Methods

### Study Design

The study is a prospective, multicenter, randomized controlled crossover trial with 2 parallel groups (Figure 1) comparing PedAMINES [13,14] with a conventional and internationally used drug infusion rate table method [15] (derived from the rule of six [16]) in the preparation of continuous drug infusion during a standardized simulation-based pediatric postcardiac arrest scenario. The infusion rate table is presented as a spreadsheet, enabling the preparation of the commonly ordered concentrations of vasoactive drugs at varying dose ranges based on the patient’s weight (Figure 2). To calculate the composition of the drug infusion, one first selects the desired drug dosage to be delivered in μg/kg/min (first column). The next step is to select the initial infusion rate in mL/h (center of the table). Finally, one calculates the milligrams of drug based on the weight of the patient to be diluted with compatible fluids (sodium chloride 0.9%, etc) in a total volume of 50 mL (first row).

The study is formatted according to the Consolidated Standards of Reporting Trials Statement for Randomized Controlled Trials of Electronic and Mobile Health Applications and Online TeleHealth (CONSORT-EHEALTH) [17] and the Reporting Guidelines for Health Care Simulation Research [18].

**Figure 1 figure1:**
[figure not shown]
Study design and flowchart per study center.

### Selection of Participants

Certified nurses are eligible for inclusion in this study. Participants must know how to prepare continuous intravenous drug injections, have previously completed a standardized 5-minute introductory course to the use of PedAMINES dispensed by an investigator of the study (SM), and be willing and able to grant written informed consent. Written informed consent will be obtained from all the participants before their voluntary involvement. Participants will be excluded if they have previously used a numeric device aimed at helping vasoactive drug preparation. Shift-working nurses will be randomly recruited on the day of the study by a blinded noninvestigator.

### Setting

The study will be conducted in 3 university hospitals and 3 smaller hospitals with a total of approximately 150,000 visits per year. The development of PedAMINES followed a user-centered and evidence-based [12] approach with emergency department (ED) caregivers as well as software developers and ergonomists. Based on pediatric resuscitation observations and focus groups, the team worked closely together to identify the key functionalities and processes to be implemented [13]. The PedAMINES app lists all the available resuscitation drugs with doses automatically adapted to the weight or age of the patient based on information entered when starting the app. At the time of the study, 15 drugs for continuous infusion and 19 drugs for direct IV injection will be listed in the PedAMINES app and at the nurse’s disposal. By a simple touch, any of the listed drugs can be selected and preparation detailed according to a standardized and simplified path. In the case of a continuous infusion, this path is composed of 3 steps: (1) drug selection, (2) dilution of the initial drug concentration, and (3) conversion of the prescribed dose rate in μg/kg/min into infusion pump rate in mL/h. For each drug, the exact amount to prepare is clearly displayed and thus avoids the necessity for calculations (Figure 3). This is based on the app’s ability to automatically calculate the optimal weight-based final infusion pump rate and describe the preparation sequence required to achieve it independently of the nurse competency in this domain. The nurse may at any time interact with the app. The user can start, pause, stop, increase, or diminish the perfusion rate. Multiple drugs can be prepared and run in parallel. All actions performed by the nurses will be sequentially saved locally on the device in historic files to preserve information that can be retrieved at any time for debriefing or medicolegal purposes. Historic files can also be erased or safely exported and saved in institutional electronic health records.

**Figure 2 figure2:**
[figure not shown]
Calculation of the Composition of Drug Infusions (Syringe Pump). Frank Shann Drug Doses [15].

**Figure 3 figure3:**
[figure not shown]
PedAMINES screenshot.

### Intervention

The scenario in this study is a short, approximately 15-minute, standardized highly realistic pediatric resuscitation simulation on a high-fidelity manikin (Laerdal SimJunior). SimJunior represents a realistic 6-year-old boy and simulates a wide range of conditions from a healthy, talking child to an unresponsive, critical patient with no vital signs. This simulator provides all functionalities that are relevant to assess the research questions, including chest compression and ventilation and vascular access, as well as realistic and interactive vital signs. To date, high-fidelity simulation has become essential to study resuscitations skills and technologies that cannot be practiced during CPR because interindividual diversity among patients and their diseases make CPR studies hard to standardize in critical situations [19]. Moreover, by standardizing the scenario and environment, we will avoid effect modifiers by preventing the influence of undesired variables on the outcomes.

Consistent with standard emergency medicine practice, we will create resuscitation teams. Two members from the study team, remaining the same along the whole study period, will assist the study participant. A Pediatric Advanced Life Support (PALS) instructor-certified emergency pediatrician will lead the resuscitation, and a nurse will assist with resuscitation by performing chest compressions and bag-valve mask ventilation according to the pediatrician instructions. Participants will be informed before the scenario starts that these 2 people are study team members. Both study team members will guide each participant through a series of predefined key steps, blinded to the participant, following a standardized resuscitation scenario (Multimedia Appendix 1). The physician will order the medications and allow progression through the scenario only once predefined milestones have been reached, regardless of the occurrence of errors or time to achieve them. The study-specific training and standardization of both study team members is ensured through their previous involvement in the pilot study [14] and by following the predefined scenario. A certified technician will operate the simulator. The study will take place during a 1-week period in every hospital and will occupy each nurse for a single 30-minute period. Thus, we anticipate a very low rate of drop-outs or loss of follow-up. To ensure the presence of participants on the day of participation, shift-working nurses will be randomly recruited 1 month before the start of the study by a blinded noninvestigator. They will be informed of the upcoming simulation study but not of its purpose and outcomes.

On the day of participation, nurses will complete a survey collecting data regarding their demographics, nursing training, and simulation and computer experience. After random allocation, each participating nurse will receive a standardized 5-minute training session on how to use the PedAMINES app. Nurses will remain unaware of specific endpoints of the study during this learning session. The simulation manikin characteristics are then presented. The nurses will then be asked to perform the pediatric resuscitation scenario, including post-ROSC. This scenario is standardized to follow the same chronological progression and range of difficulty to ensure each participant is exposed to exactly the same case, with similar challenges in decision making and treatment preparation provided on the same manikin. The uniform delivery of the scenario all along the study will minimize confounders. Study team members will only adapt to progression speed of participants through the scenario by maintaining a stressful resuscitation atmosphere. The scenario will be videorecorded and conducted in situ in the pediatric resuscitation rooms of each collaborating center to increase realism. High levels of realism are known to immerse participants in the simulated experience and prevent confounding variables that might potentially affect the way individuals perform [19]. On the day of participation, the resuscitation room will be exclusively devoted to the simulation to prevent unexpected interruption or external stimuli. Monitoring alarms will be activated to increase realism. All resuscitation equipment in the resuscitation room will be at the disposal of the nurse. In both allocation groups, the decision to use or not use any equipment will remain personal as in real life. Neither pilot testing nor repetitions will be permitted. There will be neither interventions nor educational adjuncts prior to or after the study period. Once the experiment is completed, the nurse will be required to recall and describe precisely how she prepared dopamine and norepinephrine in order to verify that the drug names and original doses prescribed by the physician were correctly understood to assess the presence of comprehension bias. Then, a quick oral debriefing, shorter than 5 minutes, on how the drugs were actually prepared and how they should have been prepared without errors will be provided to each participant by one of the study team members. The debriefing will focus on both preparation methods.

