### Sample Size

The primary objective of this study is to detect a difference in rates of medication errors between groups (with PedAMINES vs without PedAMINES). In our crossover pilot study conducted in a single university hospital, the rate of medication errors was 70% (14/20, 95% CI 46%-88%) without PedAMINES and 0% (0/20, 95% CI 0%-17%) with PedAMINES [14]. We aim to reproduce these results in 3 university hospitals and 3 smaller hospitals. The sample size was calculated to have a power of 90% to detect a difference of at least 30% in rates of medication error between intervention groups in both sets of hospitals (university and smaller hospitals). We consider that a difference of 30% in the rate of medication errors is sufficient to modify the practice. We assumed a rate of error of 15% with PedAMINES and 45% without PedAMINES. Since this study is a crossover, observations will be paired and a McNemar test will be used to compare the rate of errors between intervention groups. For the sample size calculation, we assumed that 5% of nurses will commit a medication error with PedAMINES but not without PedAMINES and that 35% of nurses will commit a medication error without PedAMINES but not with PedAMINES (Multimedia Appendix 2). With a 2-sided risk alpha of 0.05, the needed sample size is 43 nurses for each set of hospitals. Finally, 8 nurses per randomized group must be recruited in each participating center (16 nurses per center). To prevent a potential loss of power due to misspecification of assumptions, 10 nurses will be recruited per randomized group and per participating center (total sample size: 120 nurses).

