### Randomization and Blinding

Nurses will be randomized using a stratified, single, constant 1:1 allocation ratio determined with Web-based software [21]. Blinding to the purpose of the study during recruitment will be maintained to minimize preparation bias. Nurses will be unblinded after randomization. Allocation concealment will be ensured with sealed envelopes and will not be released until the nurses start the scenario. The study team members will be revealed just before the scenario starts, and videoreviewing will be done without blinding by both video reviewers but independently and blindly from one another.

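### Telling each nurse the correct preparation straight after her session creates a risk of leakage to colleagues at the same centre who have yet to face the identical scenario

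*Protocol article*

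**What the plan says.** All of the following is in the protocol article.

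- **Same case for all (Intervention).** The scenario is standardized "to ensure each participant is exposed to exactly the same case". The two test drugs are dopamine and then norepinephrine.
- **Testing window (Intervention).** "The study will take place during a 1-week period in every hospital", with one 30-minute session per nurse.
- **Debriefing (Intervention).** After the session the nurse first recalls how she prepared the drugs. A short oral debriefing "on how the drugs were actually prepared and how they should have been prepared without errors will be provided to each participant" then follows, dealing with both preparation methods.
- **Numbers (Sample Size).** Ten nurses per randomized group and centre, so 20 per centre, 60 per set of hospitals and 120 in all.
- **Protection against preparation (Randomization and Blinding).** "Blinding to the purpose of the study during recruitment will be maintained to minimize preparation bias". The Intervention section adds that nurses are not told the purpose and outcomes in advance.
- **Analysis (Sample Size).** "observations will be paired and a McNemar test will be used to compare the rate of errors between intervention groups". This takes the nurse as the independent unit.

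**The concern.** The solution to the test is handed out up to 20 times at each centre while other nurses there still have to take the same test. The scenario has fixed drugs and a fixed patient, so what a colleague passes on can be used directly. This works against the plan's own effort to keep nurses from preparing.

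Three things could suffer. First, the estimated difference in error rates could shrink. The table requires the nurse to select and calculate, whereas the app displays the amount to prepare, so prior knowledge probably helps more with the table. Second, the times to preparation and delivery could shrink in the same way. Third, results within a centre could become correlated if later nurses' performance depends on what earlier nurses told them, and the McNemar test and the Clopper-Pearson intervals make no allowance for that.

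**Working it through.** **Is testing sequential?** Twenty nurses at 30 minutes each take 20 × 0.5 = 10 hours per centre, in one resuscitation room with the same two study team members. Sessions therefore follow one another, and all nurses but the last at a centre are debriefed before a colleague is tested.

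**Inputs (Sample Size).** The target is "power of 90% to detect a difference of at least 30% in rates of medication error". "We assumed a rate of error of 15% with PedAMINES and 45% without PedAMINES". For the discordant pairs, "5% of nurses will commit a medication error with PedAMINES but not without PedAMINES", and 35% err with the table only. It follows that 15% − 5% = 10% err with both methods. Alpha is 0.05 two-sided.

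**The plan's own figure.** With p_d = 0.05 + 0.35 = 0.40 and d = 0.35 − 0.05 = 0.30:

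n = [1.960 × √0.40 + 1.282 × √(0.40 − 0.09)]² / 0.09 = 42.4, rounded up to 43.

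This reproduces the stated 43 per set. Exact McNemar power is 89.2% at 43, 92.8% at 48 (the stated minimum of 16 per centre) and 97.2% at the planned 60.

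**Leakage, by assumption.** The article gives no rate of leakage. Let f be the fraction of errors prevented, averaged over all 60 nurses of a set.

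- *Model A, only table errors prevented:* table-only = 0.35(1 − f); app-only = 0.05 + 0.10f.
- *Model B, errors with either method prevented independently with the same f:* table-only = 0.35(1 − f) + 0.10f(1 − f); app-only = 0.05(1 − f) + 0.10f(1 − f).

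| f | A: table-only / app-only | A: difference | A: power | B: table-only / app-only | B: difference | B: power |
|---|---|---|---|---|---|---|
| 0 | 35% / 5% | 30 points | 97.2% | 35% / 5% | 30 points | 97.2% |
| 0.1 | 31.5% / 6% | 25.5 points | 90.4% | 32.4% / 5.4% | 27 points | 93.9% |
| 0.2 | 28% / 7% | 21 points | 76.2% | 29.6% / 5.6% | 24 points | 88.5% |
| 0.3 | 24.5% / 8% | 16.5 points | 54.9% | 26.6% / 5.6% | 21 points | 80.9% |

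Power is exact McNemar at 60 nurses per set.

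**Correlation within a centre, by assumption.** With 20 nurses per centre the design effect on the paired difference is 1 + 19 × ICC. An ICC of 0.01, 0.02 or 0.05 gives an effective n of 60/1.19 = 50.4, 60/1.38 = 43.5 or 60/1.95 = 30.8. Approximate power is then 94.5%, 90.8% or 77.7%, against 97.4% by the same approximation without correlation.

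**The case against.** A reader might infer that the debriefing will lower errors with the table and break independence between nurses. The article supports neither as fact. Nurses would have to talk, what they pass on would have to be usable under stress, and it would have to change results. Nor does the article support the idea that leakage would be worse in smaller hospitals. It says only that staff there are less exposed to pediatric resuscitation.

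It is also tempting to say that the debriefing undoes the blinding. The blinding to purpose is promised for recruitment only, and nurses are unblinded after randomization. The Intervention section places recruitment a month before the study starts, so on that account debriefing cannot affect it. Selection of Participants places recruitment on the day of the study, and on that reading some force remains.

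That the article mentions no request for silence proves little, because such a detail may stand in the full protocol, which is not shown.

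The design limits the harm. Each nurse uses both methods in randomized order, so a leak reaches the nurse and not one arm. Model A is the harsher case, since the debriefing covers both methods. The increase from 43 to 60 per set absorbs modest leakage. At the pilot rates of 70% and 0%, even a 30% cut in table errors leaves power near 100%.

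All of this stands, and it sets the size of the point. It does not remove it, because the timing of the debriefing is stated and exposes untested colleagues to the solution.

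**Conclusion.** The point holds as a contamination risk of unknown size that comes from the stated timing of the debriefing. The probable direction is toward no difference, since the table starts from the higher error rate (45% against 15% assumed; 70% against 0% in the pilot). The likely cost is therefore an underestimated benefit and lost power. It is not a false claim of benefit, and the comparison of order groups is not confounded.

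Under the planning rates, with 10% to 30% of errors prevented, power at 60 per set lies between 90% and 55% if only table errors fall, and between 94% and 81% if both methods benefit equally. The margin above 90% is used up at about 10% leakage in the first case and between 10% and 20% in the second. Correlation within a centre is possible, but its size cannot be derived from the article. All these figures rest on assumed leakage fractions or ICCs. The power loss would matter little if the contrast is as large as in the pilot, although the estimated reduction in errors and times would still be biased.

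**What to change.** - Keep the recall check directly after each session. It does not reveal the solution.
- Defer the part of the debriefing that gives the correct preparation until the last nurse at that centre has been tested, for example as a written note.
- Ask each nurse not to discuss the case until then.
- Record the order of participation, and report error rates for both methods by test order within centre as a check for leakage.

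The cost is that feedback reaches nurses up to a week later, including those who have just made errors. A group session in place of a note would need a short second contact with shift-working staff. Sample size and primary analysis do not change.
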